### Sample size and statistical analysis

The statistical estimate of the size of the file was based on the data from previous studies in patients with congestive heart failure [6] in which was reached the difference of 13.0 + 12.9 ml in LVESV between study and control groups. α type I error of 5%, and β test strength of 80% were used to determine the required group size of 17 patients per group. When including an expected loss of 10% of patients in the 12-month follow-up (including MRI drop out), the resulting size of our group was 40 patients (20 per arm).

Continuous variables with normal distribution will be presented as mean and standard deviation (SD) and will be compared using Student 2-sample *t* test. Continuous variables with non-normal distribution will be presented as the median and range (minimum–maximum or lower and higher percentile) and will be compared using the nonparametric Mann–Whitney *U* test. Categorical variables will be presented as counts and percentages and will be compared using the χ2 or Fisher exact test. Odds ratios (OR) are expressed with 95% CI. A *p* < 0.05 will be considered significant. All statistical analyses will be performed using IBM SPSS Statistics version 22.

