### Further follow-up

The follow-up visits will be performed according to the protocol after 1, 3, 6 and 12 months (Visits 3, 4, 5 and 6) **[**Table 2**]**, and a physical examination as well as 12 lead ECG and laboratory tests (blood count + diff, clinical biochemistry, troponin I and NT-pro-BNP) will be performed during each visit and any AEs (cardiovascular death, hospitalisation due to decompensation of HF, acute MI, etc.) recorded. An echocardiographic examination will be performed during screening, and MRI examinations will take place on enrolment (Visit 1) and on the final Visit 6 in month 12. LV parameters and a percentage of total myocardial scar (TMS%) and peri-infarct border zone (PI%; PI = 2–3 SD) will be measured using delated myocardial enhancement assessment [5].

In addition, 24-h Holter ECG monitoring will be performed on enrolment (Visit 1) and after 1 month (Visit 3). Exercise tolerance using a six-minute corridor walk test and QoL (KCCQ-12) will be monitored prior to enrolment (Visit 1) and after 6 (Visit 5) and 12 months (Visit 6) **[**Table 2].

Interventional cardiologists will not be blinded to the assigned therapy, but clinical evaluation, measurement of MRI parameters and data processing will be performed by blinded, independent persons.

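### The primary LV endpoints are tested without baseline adjustment and the tested quantity (12-month value or change) is not fixed; ANCOVA on the baseline already collected settles both at almost no cost

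*Protocol article*

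**What the plan says.** The section Sample size and statistical analysis states the comparison rule by type of variable, not by endpoint. For normal data: "Continuous variables with normal distribution will be presented as mean and standard deviation (SD) and will be compared using Student 2-sample" t test. For the rest: "Continuous variables with non-normal distribution will be presented as the median and range", compared by the Mann-Whitney U test. No covariate, change score or separate rule for the primary endpoints appears, and a 95% CI is mentioned only for odds ratios.

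The same section bases the sample size on LVESV, citing previous work "in which was reached the difference of 13.0 + 12.9 ml in LVESV between study and control groups", and arrives at "the required group size of 17 patients per group". It does not say whether 12.9 ml is the SD of 12-month values or of change.

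The baseline exists. Under Further follow-up, "MRI examinations will take place on enrolment (Visit 1) and on the final Visit 6 in month 12", and Table 2 lists LV diameters, LV volumes and LV EF at the same two visits. The six-minute walk, which Methods/design places among the primary objectives, is measured at Visit 1, month 6 and month 12.

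**The concern.** A patient's LV volume at 12 months depends heavily on the volume at entry. A two-sample test of 12-month values ignores this and leaves between-patient variation in the error term. A test of change uses the baseline, but with a fixed coefficient of 1, which is optimal only when the regression slope of follow-up on baseline is 1. ANCOVA estimates the coefficient.

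Two things are therefore open in the text as written. First, the quantity compared is not named, so the link between the planning SD and the planned test cannot be verified. Second, the choice between a mean-based and a rank-based test depends on the distribution, with no criterion given. It is thus not settled in advance whether the primary result will be a mean difference in ml or a rank comparison without an estimate in ml. At stake are some power and a fixed estimand in a trial with about 17 evaluable patients per arm.

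**Working it through.** **Inputs from the article.** Difference 13.0 ml and SD 12.9 ml for LVESV (the plus sign read as ±); "α type I error of 5%, and β test strength of 80"%; 17 evaluable per arm; 10% loss; 20 per arm randomised.

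**Assumptions.** Two-sided alpha, since a one-sided test would need only 13 per arm. The correlation r between baseline and 12-month LVESV is not given, so a range is shown. Equal SD at both visits.

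**Step 1: the plan's own figure.** The normal approximation gives n = 2 × (1.96 + 0.84)² × (12.9/13.0)² ≈ 15.4, so 16. The exact t test has 78.8% power at 16 and 81.3% at 17 (noncentrality 13.0/12.9 × √(17/2) = 2.94, 32 df). The stated 17 is reproduced. Loss: 17/0.9 = 18.9, so 19 per arm or 38 in total; the plan rounds up to 40.

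**Step 2: SD under each analysis.** With s the SD at one visit:
- 12-month values: s
- change: s√(2(1−r))
- ANCOVA residual: s√(1−r²), which equals SD of change × √((1+r)/2)

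ANCOVA power is given twice: charging one df (31 instead of 32), and also allowing for expected chance imbalance in the covariate, which multiplies the variance by 1 + 1/(2n−4) = 1 + 1/30.

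**Step 3: if 12.9 ml is the SD of change** (17 per arm, 13 ml)

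| r | s (ml) | t on 12-month values | t on change | ANCOVA, df only | ANCOVA, df and imbalance |
|---|---|---|---|---|---|
| 0.5 | 12.9 | 81.3% | 81.3% | 90.8% | 89.8% |
| 0.7 | 16.7 | 59.8% | 81.3% | 87.0% | 85.9% |
| 0.8 | 20.4 | 43.7% | 81.3% | 85.1% | 83.9% |
| 0.9 | 28.8 | 24.7% | 81.3% | 83.1% | 81.9% |
| 0.95 | 40.8 | 14.7% | 81.3% | 82.2% | 80.9% |

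**Step 4: if 12.9 ml is the SD of 12-month values**

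| r | t on 12-month values | SD of change (ml) | t on change | ANCOVA, df only | ANCOVA, df and imbalance |
|---|---|---|---|---|---|
| 0 | 81.3% | 18.2 | 52.2% | 81.2% | 80.0% |
| 0.3 | 81.3% | 15.3 | 67.3% | 84.7% | 83.5% |
| 0.5 | 81.3% | 12.9 | 81.3% | 90.8% | 89.8% |
| 0.8 | 81.3% | 8.2 | over 99% | 99.7% | 99.7% |

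When the SD and the tested quantity match, the unadjusted test has its 81.3%. When they do not, it can fall well short: on raw values at r above 0.5 (Step 3), or on change at r below 0.5 (Step 4). ANCOVA stays at about 80% or more in every row.

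**Step 5: the test-selection rule.** The rule was simulated with a Shapiro-Wilk pretest (assumed, as none is named), 17 per arm and 8,000 runs. Type I error was 5.0% for normal and 5.3% for lognormal data.

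**The case against.** The strongest reply is that the design meets its target on either consistent reading. The stated objectives are to improve EF and reduce LV dimensions, which is the language of change. If 12.9 ml is also an SD of change, a t test on change has the planned 81%, and ANCOVA adds only about 1 to 10 points, with essentially no gain at r = 0.95 once covariate imbalance is allowed for. This stands, and it limits the size of the point. It does not defend the text, which states a method and leaves the tested quantity open.

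Four stronger readings may tempt a reader. None is supported.

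- *The trial has only 25% to 44% power.* Those figures require a change SD combined with a test on raw 12-month values at r of 0.9 or 0.8. The article states neither half of that combination, and gives no r.
- *Chance baseline imbalance biases the result.* Under randomisation the unadjusted comparison is unbiased and its standard error covers chance imbalance. The article says nothing about stratification either way, so its absence cannot be asserted.
- *Switching tests inflates type I error.* The simulation shows 5.0–5.3%. The two tests do fall on opposite sides of 0.05 in about 5–6% of trials when an effect exists, but in only 2.2% under the null.
- *ANCOVA secures the trial's power.* It does not repair an optimistic effect. At the pooled LVESV effect of 6.37 ml quoted in the Discussion, with SD 12.9 ml, the unadjusted test has 28.7% power at 17 per arm.

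One further point favours the plan's rank test. With lognormal data in the same simulation, Mann-Whitney had 93% power against 82% for the t test. Skewed variables therefore need a transformation chosen in advance, not an untransformed linear model.

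**Conclusion.** The concern holds as a matter of efficiency and of an unfixed estimand. The stated analysis is valid, but a better one is available from data already scheduled. With matched readings the gain at 17 per arm and 13 ml is from 81% to about 82–91% (12.9 ml an SD of change, r 0.95 to 0.5), or to about 91% at r = 0.5 and over 99% at r = 0.8 (12.9 ml an SD of 12-month values). Allowing for covariate imbalance lowers these by about one point at most. If the SD and the tested quantity do not match, the written method could fall to 60%, 44% or 25% at r = 0.7, 0.8 or 0.9, and ANCOVA removes that exposure. All values of r are assumptions, as is the meaning of 12.9 ml. This should be fixed, as a nearly free improvement; it does not invalidate the design.

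**What to change.** Replace the general rule, for the primary endpoints, with a stated model:

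- Analyse each primary LV endpoint and the six-minute walk by ANCOVA of the 12-month value on arm, with that variable's own Visit 1 value as covariate. Report the adjusted mean difference with 95% CI. This does not decide which endpoint is the main one; that is a separate matter.
- Because Methods/design has ICD patients who cannot undergo MRI measured by echocardiography, use the same modality at both visits within a patient and include modality (MRI or echo) in the model.
- Log-transform variables expected to be skewed, such as NT-proBNP, as a choice made in advance.
- Keep a rank-based test as a sensitivity analysis only, and drop selection of the primary test by distribution.
- State whether 12.9 ml is the SD of change or of 12-month values.

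Cost: a paragraph of text and no new measurements. The baseline covariate takes one degree of freedom, about 0.1 point of power if r = 0, or about 1.3 points (81.3% to 80.0%) when expected covariate imbalance is counted. The modality term takes one more degree of freedom. The change should be made before any unblinded analysis.

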### Aim

The aim of this prospective randomised study is to assess the efficacy of the retrograde application of non-selected BMAC in patients with HFREF of ischemic aetiology. The evaluated preparation is concentrated BMAC, obtained using *Harvest SmartPReP2* (Harvest Technologies, Plymouth, MA, USA).

Our assumption is that non-selected BMAC administrations will lead to improvements in the left ventricular ejection fraction (LV EF), the left ventricular end-systolic and end-diastolic diameters and volumes (LVESd/EDd and LVESV/EDV) compared to standard HF therapy. Furthermore, it will be associated with improved exercise tolerance in the six-minute corridor walk test, a decrease in NYHA and CCS classes and an improvement in the life quality (QoL) of patients. At the same time, this therapy will not increase the incidence of severe ventricular arrythmias detected by 24-h ECG Holter monitoring.

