## Methods/design

The study population will be a total of 40 patients with established CAD and left ventricular systolic dysfunction with an EF of ≤40% and HF in the NYHA class 3. CAD will be demonstrated based on previous coronary angiography (myocardial infarction > 6 months, presence of significant coronary stenosis, previosu revascularisation) or Tc SPECT (perfusion defects). The patient follow-up duration will be 12 months.

Patients have been on standard HF therapy for 3 months and in a stabilised state for at least 1 month, before enrolling in the clinical study. A list of inclusion and exclusion criteria is provided in Table 1.

**Table 1 Tab1:** Inclusion and exclusion criteria

Inclusion criteria:	
• Patients with chronic heart failure and left ventricular ejection fraction ≤40% with coronary artery disease and with symptoms of heart failure in the NYHA class 3 on standard heart failure therapy for 3 months and in a stabilised state for at least 1 month,	
• Age 40–80 years	
• Informed, written consent by the patient	
• Ability to comply fully with the study protocol	
• Negative pregnancy test (and effective contraception) in women with childbearing potential	
Exclusion criteria:	
• Previous bone marrow disease (especially myelodysplastic syndrome or non-Hodgkin’s lymphoma)	
• Repeated acute coronary syndrome <1 month	
• CRT device with LV lead in CS	
• Active infection or ATB treatment <1 week	
• Previous malignant ventricular arrhythmias without ICD implantation	
• Anemia (HTC ≤ 28%), leukocytosis (≥14.000/mm^3^) or thrombocytopenia (≤50.000/mm^3^)	
• Previous bleeding diathesis	
• Need for hematopoietic growth factor treatment (e.g. erythropoetin, G-CSF)	
• Impossibility of aspiration 240 ml of bone marrow	
• Hepathopathy or cirrhosis (bilirubin, ALT or AST ≥2,5x ULN)	
• Chronic kidney disease >3b stage (eGFR <45 ml/min/1.73m^2^)	
• Uncontrolled hypertension	
• Need for high dose (> 7.5 mg/day) corticotherapy within the next 6 months	
• Inability to stop anticoagulation therapy (> 72 h) before bone marrow aspiration	
• Known malignancies requiring actino or chemotherapy, or previous actinotherapy	
• Patients with a BMI > 40	
• Known allergy to contrast agents	
• Other comorbidities with a life expectancy of 6 months	

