Patients will be randomised 1:1 to one of the following treatment methods: either retrograde BMAC administration via coronary sinus or the control group with standard HF therapy. Patients randomised to the control group will not undergo bone marrow collection, due to ethical reasons. Only standard right heart catheterisation will be performed as sham procedure.

The primary objectives of the clinical study are to improve the LV EF and reduce the LVESd/EDd and LVESV/EDV assessed by magnetic resonance imaging (MRI), and to improve exercise tolerance in the six-minute corridor walk test.

The secondary objectives include identifying the occurrence of severe ventricular arrhythmias according to 24-h ECG Holter monitoring, improving on the NYHA and CCS classes, reducing hospitalisations due to decompenzation of HF, assessing the impact on QoL of patients using the Kanas City Cardiomyopathy Questionare (KCCQ-12) and ensuring the safety of BMAC retrograde administration via coronary sinus by evaluating all adverse events (AE).

All patients will continue on the standard HF treatment during the clinical follow-up (ACE inhibitor/ATII blockers, beta-blockers, MRA, diuretics) and medication necessary for secondary CAD prevention (ASA/clopidogrel, statins). The monitored parameters will be measured echocardiographically in ICD-implanted patients not able to undergo MRI. Patient with cardiac resynchronization therapy (CRT) device (or CRT-ICD) with LV lead placed in CS will not be included. We also not include patients with known contrast allergy.

Written informed consent was obtained from each patient before enrollment in the study. The study protocol complied with the Declaration of Helsinki and was approved by the Ethics Committee of University Hospital Ostrava, Czech Republic. The study was registered at ClinicalTrials.gov (https://clinicaltrials.gov; NCT03372954).

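### NYHA and CCS class are ordered outcomes with a directional hypothesis, but the only test rule that covers them ignores class order when three or more classes are compared

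*Protocol article*

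**What the plan says.** Among the secondary objectives, the Methods/design section of the protocol article lists "improving on the NYHA and CCS classes". The Aim section gives the direction: the treatment is expected to bring "a decrease in NYHA and CCS classes". Every patient enters with "HF in the NYHA class 3". Table 1 sets no limit on CCS class at entry.

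The section on sample size and statistical analysis sorts variables into three kinds. Normal continuous variables get the t test. For the second kind, "Continuous variables with non-normal distribution will be presented as the median and range", and these are compared with the Mann-Whitney U test. For the third, "Categorical variables will be presented as counts and percentages and will be compared using the χ2 or Fisher exact test". The section also plans odds ratios with 95% confidence intervals. It names no test for ordered categories, does not mention NYHA or CCS, and does not say whether class will be analysed in full or as improved or not.

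**The concern.** NYHA and CCS are ordered scales and the stated hypothesis is a shift in one direction. On a table with three or more columns, χ2 and the extended Fisher test ask only whether the two distributions differ in any way. This has two consequences.

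- **Lost power.** The test spreads its sensitivity over departures that are not of interest. With about 18 evaluable patients per arm there is little information to spare.
- **Ambiguous significance.** A small p value can come from a wider spread, with more patients better and more patients worse, which is not the improvement the protocol expects.

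The plan already contains a test that uses order, but confines it to continuous data.

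**Working it through.** **1. The plan's own sample size.** Inputs, from the statistical section: "the difference of 13.0 + 12.9 ml in LVESV between study and control groups", with 12.9 ml read as the SD, and "α type I error of 5%, and β test strength of 80% were used". Sidedness is not stated; two-sided is assumed.

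- n per arm = 2(1.960 + 0.842)² × (12.9/13.0)² = 2 × 7.85 × 0.985 = 15.5, so 16. The t-test version needs 16.5, so 17, as stated.
- With 10% loss: 17/0.9 = 18.9, so 19 per arm or 38 in total. The plan rounds up to 40.
- Expected evaluable number: 20 × 0.9 = 18 per arm.

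The figure reproduces. It is based on LVESV; no power is stated for NYHA or CCS.

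**2. Why degrees of freedom matter.** Take a shift that gives a 1-df ordered test 80% power (noncentrality 7.85). At the same noncentrality, a 2-df test (three classes) has 71% power and a 3-df test (four classes) 64.5%. The relative losses are 1 − 71/80 = 11% and 1 − 64.5/80 = 19%. Where the 1-df test has only 30% power, the losses are 23% and 34%.

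**3. Simulation at this trial's size.** Class distributions and effects are assumptions. The treated distribution is obtained from the control distribution by a common cumulative odds ratio (OR). Tests are two-sided at 5%, and the Mann-Whitney test is tie-corrected.

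*18 per arm; control NYHA I/II/III/IV 5/30/55/10%; collapsed means I-II v III-IV:*

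| OR | χ2, full table | Fisher, collapsed | χ2 uncorrected, collapsed | Mann-Whitney |
|---|---|---|---|---|
| 3 | 21% | 28% | 39% | 38% |
| 4 | 37% | 43% | 57% | 57% |
| 5 | 48% | 55% | 68% | 69% |

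Relative loss of full-table χ2: 1 − 21/38 = 45%; 1 − 37/57 = 35%; 1 − 48/69 = 30%. Collapsed χ2 loses essentially nothing. Collapsed Fisher loses 26%, 25% and 20%, because it is conservative here: its null rejection rate is about 2%, against just under 5% for Mann-Whitney and 5.6% for collapsed χ2.

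*20 per arm, varying the number of classes and the effect:*

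| Control distribution | OR | χ2, full table | Mann-Whitney | Relative loss |
|---|---|---|---|---|
| Four classes, 5/35/50/10% | 3 | 25% | 43% | 42% |
| | 4 | 38% | 61% | 37% |
| | 6 | 64% | 82% | 22% |
| | 10 | 86% | 96% | 11% |
| Three classes, 35/55/10% | 3 | 30% | 42% | 28% |
| | 4 | 45% | 58% | 22% |
| | 6 | 68% | 78% | 14% |
| | 10 | 86% | 93% | 7% |
| Two classes, 30/70% | any | same | same | 0% |

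Losses are taken from unrounded powers. With two classes, uncorrected χ2 and Mann-Whitney coincide.

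A five-class CCS distribution (30/25/25/15/5%) was run for small effects only: 48% loss at OR 3 with 17 per arm, and 50 to 53% at OR 2, where the rank test itself has only 19 to 23% power.

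**4. Significance without improvement.** Assume control 2/18/70/10% and treated 5/35/25/35%, 18 per arm. Class I-II rises from 20% to 40%, but class IV also rises, from 10% to 35%. Full-table χ2 is significant in 67% of trials and Mann-Whitney in 6%.

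**The case against.** The strongest reply is that the trial may never test a full class table. The objective is worded as improvement, everyone starts in NYHA 3, and odds ratios are planned. All of this suits a binary improved-or-not analysis, and for NYHA that is I-II against III-IV. Uncorrected χ2 on that split is allowed by the plan and, as the first table shows, has the same power as the rank test. This stands. A reader might infer that collapsing NYHA wastes information; the scenario examined does not support that, and the shortfall against collapsed Fisher is Fisher's conservatism.

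Three limits apply to the reply. The article does not say that it will collapse, so the choice of split, and of χ2 or Fisher, is open. CCS has no common starting class and may span several, so no single cut has the natural standing that I-II has for NYHA, and a poorly placed cut loses power. An improved-or-not split also cannot tell a patient who stays in class III from one who worsens to IV.

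It can also be said that test assignment by endpoint belongs in the full protocol or analysis plan. That would answer a complaint that detail is missing. Here the article states a general rule whose natural reading covers NYHA and CCS, and the rule fits them badly. That they fall under it is still an inference, since neither is named.

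Finally, χ2 and Fisher are valid tests of any difference, so this is a matter of efficiency and interpretation, not of false-positive error.

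**Conclusion.** The point holds in a limited form. As written, the only rule that covers NYHA and CCS ignores class order when three or more classes are compared, although the hypothesis is directional. Under assumed distributions with 17 to 20 per arm, full-table χ2 loses roughly 10 to 45% of the rank test's power. The edges fall outside that range: 7% with three classes and a very large effect, and about 50% with five classes and a small one. The loss is zero when only two classes occur.

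A reader might infer a general loss of a third or more. The documents do not support this. They give no month-12 distribution and no expected effect, and a loss of that size arises mainly with four or more occupied classes and an effect for which the rank test itself has about 60% power or less. Since all patients enter in NYHA 3, follow-up NYHA may occupy only two or three classes.

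The outcomes are secondary. The primary MRI endpoints and the sample size are not touched.

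**What to change.** Add one sentence to the statistical section: NYHA and CCS class at month 12 are compared between arms with the tie-corrected Mann-Whitney test, or with proportional-odds regression reporting a common odds ratio and 95% confidence interval. If regression is chosen, include baseline CCS as a covariate for CCS; NYHA needs no baseline term because all patients enter in the same class. Restrict χ2 and Fisher to nominal and binary variables. If an improved-or-not summary is also wanted, define the split and name the test in advance.

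The cost is that sentence. It needs no extra patients or data, and the Mann-Whitney test is already in the plan. Proportional-odds regression adds the assumption of a common odds ratio across cut-points; the rank test does not. If only two classes turn out to be occupied, the rank test coincides with uncorrected χ2 and nothing is lost.

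### The odds ratio is the only effect measure given a confidence interval; with 20 per arm it has no finite upper limit for uncommon safety outcomes whenever the control arm is event-free

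*Protocol article*

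**What the plan says.** The section Sample size and statistical analysis of the Protocol article deals with binary outcomes in two sentences. The first gives presentation and test: "Categorical variables will be presented as counts and percentages and will be compared using the χ2 or Fisher exact test". The second gives the effect measure: "Odds ratios (OR) are expressed with 95% CI". It names no method for the interval and no risk difference or risk ratio.

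The same section fixes the arm size: "the resulting size of our group was 40 patients (20 per arm". Allocation is equal.

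The outcomes concerned are among the secondary objectives in Methods/design. They include "identifying the occurrence of severe ventricular arrhythmias according to 24-h ECG Holter monitoring", hospitalisation for decompensated heart failure, and an evaluation of all adverse events. Further follow-up lists cardiovascular death and acute MI as examples of events to be recorded. The Aim section states the expectation that the therapy will not raise the incidence of severe ventricular arrhythmias on Holter monitoring. Table 2 schedules one Holter after treatment, at month 1.

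**The concern.** A statement that a therapy does not increase harm rests on the upper limit of the treatment contrast. A non-significant p-value in 20 v 20 patients does not show that harm is absent. The plan attaches an interval to one contrast only, the odds ratio, and that measure breaks down when an arm has no events. In arms of 20 this is an ordinary result for an uncommon outcome. The safety comparison could then report that no significant difference was found, with no bound on how large an excess remains possible.

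**Working it through.** **The plan's own figure.** The arm size comes from LVESV, not from any binary outcome: "the difference of 13.0 + 12.9 ml in LVESV between study and control groups" (the plus sign read as ±), with 5% alpha (taken as two-sided) and 80% power, leading to "the required group size of 17 patients per group". The normal approximation gives n = 2 × (1.960 + 0.842)² × (12.9/13.0)² = 2 × 7.849 × 0.985 = 15.5, so 16. The t-test version gives 16.48, so 17, as stated. Allowing for 10% loss, 17/0.90 = 18.9, so 19; the plan uses 20. The arm size is not in dispute.

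**How often an arm is event-free.** Inputs: n = 20 per arm (document) and an equal event risk p in both arms (assumption; the document gives no rate for any binary secondary outcome). Let q = (1 - p)^20 be the probability that a given arm has no event.

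| Assumed p | Control arm empty: q | At least one arm empty: 1 - (1 - q)² | Both arms empty: q² |
|---|---|---|---|
| 2% | 0.668 | 0.890 | 0.446 |
| 5% | 0.358 | 0.588 | 0.129 |
| 10% | 0.122 | 0.228 | 0.015 |
| 20% | 0.012 | 0.023 | <0.001 |

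With 17 evaluable per arm, the probability of at least one empty arm rises to 0.66 at 5% and 0.31 at 10%.

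**What the odds ratio then gives.** The usual interval uses SE(log OR) = √(1/a + 1/b + 1/c + 1/d), which does not exist if any cell is zero. An exact conditional interval does exist. The table sets it beside the Newcombe risk difference, with odds ratios and differences as BMAC relative to control.

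| BMAC v control | Odds ratio (exact 95% CI) | Risk difference, points (Newcombe 95% CI) | Fisher p |
|---|---|---|---|
| 0/20 v 0/20 | 0/0 (0 to ∞) | 0 (-16.1 to +16.1) | 1.00 |
| 2/20 v 0/20 | ∞ (0.19 to ∞) | +10 (-7.7 to +30.1) | 0.49 |
| 3/20 v 0/20 | ∞ (0.43 to ∞) | +15 (-3.8 to +36.0) | 0.23 |
| 4/20 v 0/20 | ∞ (0.71 to ∞) | +20 (-0.1 to +41.6) | 0.11 |
| 0/20 v 4/20 | 0 (0 to 1.42) | -20 (-41.6 to +0.1) | 0.11 |

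One Newcombe interval in full, for 2/20 v 0/20. The Wilson limits are 0.028 to 0.301 for 2/20 and 0 to 0.161 for 0/20, where 0.161 = 1.96²/(20 + 1.96²). Lower limit: 0.10 - √((0.10 - 0.028)² + 0.161²) = -0.077. Upper limit: 0.10 + √((0.301 - 0.10)² + 0²) = 0.301.

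**Reading.** The exact interval loses its upper limit when the control arm is empty, the column headed q in the first table: 67%, 36%, 12% and 1% at the four assumed risks. An empty BMAC arm facing events in the control arm is less of a problem, because the upper limit is then finite (1.42 in the last row).

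**The case against.** The strongest reply is that this is detail for the analysis plan. The text is a condensed paragraph in a journal article. An odds ratio with a 95% interval is conventional, the article does not say the interval is the log-odds-ratio one, and the handling of zero cells is commonly settled elsewhere. That stands as far as the interval method goes, and its absence is no fault. The choice of effect measure, however, is made in the article, and it is this choice that leaves no upper limit when the control arm is empty, even with the exact method.

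Adding 0.5 to each cell does give a finite limit. For 2/20 v 0/20, OR = (2.5 × 20.5)/(0.5 × 18.5) = 5.5 and SE = √(1/2.5 + 1/18.5 + 1/0.5 + 1/20.5) = 1.58, so the interval is 0.25 to 123. That upper limit depends heavily on the added constant and is too wide to help.

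A reader might infer more than the documents support:

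- *That the odds ratio is undefined whenever an arm is empty.* It is 0/0 only when both arms are empty (13% at a 5% risk, 1.5% at 10%). Otherwise it is 0 or infinite, and an exact interval exists.
- *That these outcomes end with no effect estimate.* The plan also reports counts and percentages, which give the observed risk difference directly, and Fisher's test copes with zero cells. What is missing is an interval for that difference.
- *That outcomes without a finite odds ratio will go unreported.* Nothing says so; Methods/design commits to evaluating all adverse events.
- *That most binary outcomes are affected.* This depends on rates the document does not give. The problem nearly disappears at a risk of 20%, and heart failure hospitalisation or a change in NYHA class may well be that common.

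It is also fair to say that an interval of ±16 points for 0 v 0 mostly reflects the small sample. But that is what a reader of a no-increase statement needs to see.

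**Conclusion.** The point holds in limited form, as a cheap improvement. The only effect measure given an interval cannot bound excess harm when the control arm has no events. The chance of that is 67%, 36%, 12% and 1% at risks of 2%, 5%, 10% and 20%, and the chance of at least one empty arm is 89%, 59%, 23% and 2%. These figures assume equal risks in the two arms and 20 evaluable patients each, and the risks themselves are assumptions. The only related rate in the document, coronary sinus injury at 0.06 to 0.6% (Discussion), concerns a procedure that the control arm does not undergo, so it does not inform a comparison between arms.

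The consequence falls on uncommon secondary and safety outcomes, chiefly the expectation of no increase in severe ventricular arrhythmias. The primary MRI endpoints, the sample size, the choice of tests and common binary outcomes are unaffected.

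**What to change.** Add to Sample size and statistical analysis:

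*For binary outcomes, including all safety outcomes, the risk difference between arms is reported with a 95% score-based (Newcombe or Miettinen-Nurminen) confidence interval for every outcome, whatever the cell counts; the odds ratio is reported in addition, with an exact interval when a cell is zero.*

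Applying the rule whatever the counts keeps the reported measure from depending on the data. It keeps the planned odds ratio and needs no extra patients or data. The cost is minor programming: if the named software version does not supply the interval, the Newcombe limits follow from the short formula shown above. The change does not make the trial large enough to rule out moderate harm, but it shows how much harm has not been ruled out.
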